#### 2.9.7. Integrated Environmental, Ecological, and Human Health Analyses

Meteorological, biological, and clinical data will be integrated to examine linkages between environmental conditions, biodiversity, and human health outcomes. This combined analysis will allow evaluation of whether observed physiological responses are mediated by changes in temperature, air quality, or ecological activity at the site. Examples of this may include the reduction in temperature caused by exposure to the microforest, leading to an improvement in heart rate variability and blood pressure, as well as changes or differences in VOC exposure or cortisol levels due to greenness exposure.

### 2.10. Power Calculation

Power calculations were conducted using PASS 2023 (NCSS, LLC) to evaluate expected differences in slope of outcome measures between two walking sites (microforest vs. parking lot). The primary outcomes are blood pressure and heart rate variability (SDNN). Based on a previous walking study with a similar study design [64], we expect HRV (SDNN) values of 31.0 ± 6.7 and 22.6 ± 6.7 for the microforest walking and parking lot walking, respectively. Based on these effect sizes and using α = 0.05/2 = 0.025 to account for multiple comparisons, we expect that we will have >90% power with a sample size of *n* = 50 for HRV. If recruitment yields only *n* = 40 participants, power remains above 85% for both primary outcomes. Thus, this study is adequately powered to detect clinically meaningful differences in cardiovascular stress responses, even with modest variation in effect sizes. Subgroup analyses (e.g., by sex or pollutant exposure strata) are also expected to retain sufficient power. These estimates align with sample sizes used in previous studies employing similar protocols, including Lee et al., *n* = 43 [55], Koselka et al., *n* = 38 [51], and de Brito et al., *n* = 23 [54]. Collectively, these benchmarks provide confidence in the adequacy of the planned sample size for robust inference.

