To analyze soil microbiome data, sample inference from amplicon data will first be performed using the DADA2 denoising workflow [64]. DADA2 generates amplicon sequence variant (ASV) tables, which allow for finer resolution than older OTU grouping methods [65]. Bacterial ASVs will then be annotated using the SILVA SILVA_SSU_r138_2019 database [66], and fungal ASVs will be annotated using the UNITE sh_general_release_all_10.05.2021 database [67]. Changes in microbiome community composition over time and in response to other soil properties (e.g., soil nutrients and heavy metal concentrations) will be assessed using principal components analysis. Changes in community diversity over time will be assessed using ANOVA. Indicator species analysis will be performed to identify particular microbial species associated with increased soil health factors and greenness.

Tree inventory data will be analyzed with i-Tree Eco (v6.1.47) to estimate carbon storage and sequestration, pollution removal, oxygen production, and prevented runoff. The results will be aggregated to characterize overall ecosystem services provided by the microforest.

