## 3. Expected Results

The creation of the [name] Microforest as part of the Green Oasis (GRO) Project provides a structured framework to examine how targeted greening interventions influence both environmental and human health outcomes in dense urban cores. The randomized crossover design allows comparison of individual-level physiological responses when participants are exposed to two distinct urban environments: a densely vegetated microforest and a nearby impervious parking lot. By combining high-resolution environmental monitoring with continuous physiological measurements, this study is designed to determine whether modifications in microclimate are associated with measurable changes in cardiovascular and stress biomarkers. We expect that the microforest environment will exhibit measurable differences in local environmental conditions relative to the impervious comparison site. These differences may include lower ambient temperature, increased relative humidity, reduced solar radiation exposure, and potentially lower concentrations of air pollutants. Continuous meteorological monitoring and personal environmental exposure measurements collected during participant visits will allow these environmental differences to be quantified at the spatial and temporal scale of participant exposure.

The primary physiological outcomes of this study are HRV and blood pressure, both of which are well-established indicators of autonomic cardiovascular regulation and acute cardiovascular stress. Within the crossover design of the GRO study, we therefore expect that exposure to the cooler and more vegetated microforest environment may be associated with higher HRV values and modest reductions in systolic and diastolic blood pressure compared with the impervious parking lot condition. Such findings would be consistent with improved autonomic balance and reduced cardiovascular stress during exposure to the vegetated environment.

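### Section 2.10 supports power only for the paired mean SDNN contrast; the blood pressure, slope and subgroup power claims have no stated basis

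*Protocol article*

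**What the plan says.** Section 2.10 describes the calculation as one made "to evaluate expected differences in slope of outcome measures between two walking sites (microforest vs. parking lot". The only effect size in it is for HRV: "we expect HRV (SDNN) values of 31.0 ± 6.7 and 22.6 ± 6.7 for the microforest walking and parking lot walking, respectively". The significance level is "α = 0.05/2 = 0.025 to account for multiple comparisons".

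Three claims follow:

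- For HRV at n = 50: "we expect that we will have >90% power with a sample size of" 50.
- For n = 40: "participants, power remains above 85% for both primary outcomes". The two primary outcomes are blood pressure and SDNN.
- "Subgroup analyses (e.g., by sex or pollutant exposure strata) are also expected to retain sufficient power".

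On blood pressure, Section 3 says only that the authors expect "modest reductions in systolic and diastolic blood pressure compared with the impervious parking lot condition".

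Section 2.9.2 sets out the tests that these claims must serve: a mixed model with a treatment effect, a temperature-by-treatment interaction, and tests of effect modification by sex and particulate matter. The abstract repeats that sensitivity is adequate at about 40–50 participants.

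**The concern.** Power statements decide how a null result is read. If the plan says that blood pressure, the slope comparison and the subgroups were all adequately powered, a null finding on any of them will be taken as evidence of no effect.

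The section prints inputs for one quantity, mean SDNN, and conclusions for four: mean SDNN, blood pressure, a slope difference and subgroups. Mean levels say nothing about a slope difference, which also needs an expected slope at each site, the spread of temperature and the residual variation. For blood pressure a numerical result is printed with nothing behind it, and the text does not say whether it means systolic or diastolic pressure.

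**Working it through.** **Inputs from Section 2.10.** Mean SDNN 31.0 and 22.6, so the difference is 8.4; SD 6.7 at each site; alpha 0.025; n = 50 or 40. **From Table 3:** 16 men and 24 women in Wave 1, 20 men and 30 women in Wave 2. **Assumed, because not stated:** a two-sided test and a within-person correlation ρ, shown mainly over 0 to 0.5.

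**1. The plan's own SDNN figures.** For a paired t-test, SD of the difference = 6.7 × √(2(1 − ρ)), and the noncentrality is 8.4 / SD of the difference × √n.

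| ρ | SD of difference | Standardised difference | Power, n = 40 | Power, n = 50 |
|---|---|---|---|---|
| −1 (worst case) | 13.4 | 0.63 | 94.4% | 98.1% |
| 0 | 9.48 | 0.89 | 99.93% | 99.99% |
| 0.5 | 6.70 | 1.25 | >99.99% | >99.99% |

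If 40 or 50 people were instead split into two parallel groups, the t-test would have 94.4% or 98.1% power. The SDNN floors (above 85% and above 90%) hold in every variant, but the inputs do not show how those particular floors were chosen.

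**2. Slope.** No slope, temperature range or residual SD is given, so power for the temperature-by-treatment interaction cannot be computed. If the word refers to change over time instead, the inputs for that are absent too.

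**3. Blood pressure.** The stated figure cannot be reproduced. Working backwards, exactly 85% power at n = 40 (paired t, two-sided alpha 0.025) needs a standardised within-person difference of about 0.54 (0.536 before rounding). In mmHg this depends on an SD that the article does not give:

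| Assumed SD of difference (mmHg) | Difference needed = 0.536 × SD (mmHg) |
|---|---|
| 5 | 2.7 |
| 8 | 4.3 |
| 10 | 5.4 |
| 12 | 6.4 |

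Whether the modest reduction expected in Section 3 reaches these values cannot be judged from the article.

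**4. Subgroups, SDNN within one sex** (same paired formula, alpha 0.025).

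| Group | ρ = 0 | ρ = 0.5 |
|---|---|---|
| 16 men | 84% | 99% |
| 20 men | 93% | 99.9% |

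**5. Effect modification by sex, SDNN.** This is a two-sample t-test on the within-person differences, with SE = SD of the difference × √(1/men + 1/women). For 20 men and 30 women at ρ = 0, SE = 9.48 × √(1/20 + 1/30) = 2.73. An interaction of half the main effect is 4.2, so the noncentrality is 4.2 / 2.73 = 1.54.

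| Interaction size | 20 vs 30, ρ = 0 | 20 vs 30, ρ = 0.5 | 16 vs 24, ρ = 0 | 16 vs 24, ρ = 0.5 |
|---|---|---|---|---|
| Equal to the main effect (8.4) | 77% | 98% | 66% | 93% |
| Half the main effect (4.2) | 23% | 45% | 18% | 36% |

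At ρ = 0.7 the half-size interaction with 20 men and 30 women reaches 69%.

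**6. Source of the inputs.** Section 2.10 attributes the SDNN values to reference [64], a walking study. Section 2.9.6 gives the same number to a sequencing method: "sample inference from amplicon data will first be performed using the DADA2 denoising workflow [64]". As numbered, the source of the only effect size cannot be traced.

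**The case against.** The best defence is that nothing printed is shown to be false. The percentages are lower bounds, and 99.9% satisfies both above 85% and above 90%. The sentence for n = 40 is one floor covering two outcomes and may simply be set by blood pressure. A condensed article may leave the blood pressure inputs to the full protocol. The stated SDNN effect does support within-sex tests.

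Most of this stands, and it rules out three stronger readings.

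- *That the plan's own figures contradict the subgroup claim.* A reader could take 85% at n = 40 as exact and get 39% power in 16 men and 59% in 24 women. But the text gives a floor, not a value, and the only stated effect size gives 84–99% for those 16 men.
- *That the 85% figure comes from an undisclosed weaker effect.* This is possible, but it is conjecture.
- *That blood pressure is underpowered.* The article does not show this. With an SD of differences of 5 mmHg, a difference of 2.7 mmHg would be enough.

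The defence does not reach the mismatch between a slope calculation and mean-level inputs, which is in the article's own wording. Nor does brevity fully explain a printed result for blood pressure beside printed inputs for SDNN only. Support for within-sex tests also does not carry over to the effect-modification tests that Section 2.9.2 actually plans.

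**Conclusion.** The point holds in this form: the power shown in Section 2.10 belongs to the paired mean SDNN contrast and to nothing else.

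- **SDNN:** the claims are true but uninformative.
- **Blood pressure:** the claim cannot be checked.
- **Temperature-by-treatment interaction:** no power basis is stated.
- **Subgroups:** the blanket claim is unsupported, and it is not defensible for effect modification. A sex interaction half the SDNN effect has about 23–45% power at 20 versus 30 and 18–36% at 16 versus 24.

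The SDNN and interaction figures assume a two-sided alpha of 0.025, an SD of 6.7 at both sites and correlation 0 to 0.5. The blood pressure values in mmHg rest on assumed SDs. The duplicate use of reference [64] is a minor point: the reference list is not shown, so it cannot be said which use is wrong.

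**What to change.** 1. Restate Section 2.10, and the matching abstract sentence, as power for the paired mean SDNN contrast, giving the correlation and sidedness used.
2. For blood pressure, name the measure and give the assumed difference and SD of the within-person difference, for example from Wave 1 and 2 data. Otherwise state the minimum detectable effect: about 0.54 SD of the within-person difference for 85% power at n = 40, two-sided alpha 0.025.
3. Remove the reference to slope, or power the temperature-by-treatment interaction explicitly with its own inputs.
4. Replace the subgroup sentence with a statement that effect-modification and slope-interaction analyses are exploratory and not powered for interactions smaller than the main effect.
5. Reconcile reference [64] between Sections 2.9.6 and 2.10.

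The cost is text, plus a variance estimate from data already collected if that route is taken for blood pressure. No extra participants are needed. Some claims become less favourable, and null results for blood pressure, slope and subgroups could then be read for what they are.

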### 2.11. Maintenance and Ongoing Work

The [name] Microforest is a unique urban green space that requires intensive early maintenance to ensure establishment. An automated irrigation system was installed to support the survival of newly planted trees, shrubs, and groundcovers, with schedules adjusted according to rainfall. The site is inspected regularly by an in-house arborist and receives weekly maintenance visits from the construction contractor. Plants that die within the first years will be replaced; over the long term, natural competition for resources will be allowed to occur, resulting in some expected mortality. Tree mortality is anticipated at 8–11% during the establishment phase, increasing in later years as canopy closure leads to shading stress. Understory trees will be planted periodically to replace those lost to competition, maintaining species diversity and structural complexity.

### 2.12. Data Dissemination and Data Sharing

Data analysis will be conducted within a secure research environment. Upon study completion, datasets, analytic code, and statistical models will be made available through GitHub (3.19.3) to ensure transparency and reproducibility. Findings from the GRO Project will be disseminated through peer-reviewed publications and presentations at national and international conferences. In addition to academic dissemination, updates will be shared with stakeholders and the community. The Urban Design Studio website will continue to post blog updates on project progress and findings. Engagement efforts will also include outreach to urban planners, landscape architects, developers, and policymakers in Louisville and beyond. The [name] Microforest functions both as a public park and as an “urban laboratory,” providing a platform for future research on greening, health, and resilience. Potential future studies may extend to topics such as stormwater management, biodiversity, social cohesion, and climate adaptation.

## 3. Expected Results

The creation of the [name] Microforest as part of the Green Oasis (GRO) Project provides a structured framework to examine how targeted greening interventions influence both environmental and human health outcomes in dense urban cores. The randomized crossover design allows comparison of individual-level physiological responses when participants are exposed to two distinct urban environments: a densely vegetated microforest and a nearby impervious parking lot. By combining high-resolution environmental monitoring with continuous physiological measurements, this study is designed to determine whether modifications in microclimate are associated with measurable changes in cardiovascular and stress biomarkers. We expect that the microforest environment will exhibit measurable differences in local environmental conditions relative to the impervious comparison site. These differences may include lower ambient temperature, increased relative humidity, reduced solar radiation exposure, and potentially lower concentrations of air pollutants. Continuous meteorological monitoring and personal environmental exposure measurements collected during participant visits will allow these environmental differences to be quantified at the spatial and temporal scale of participant exposure.

The primary physiological outcomes of this study are HRV and blood pressure, both of which are well-established indicators of autonomic cardiovascular regulation and acute cardiovascular stress. Within the crossover design of the GRO study, we therefore expect that exposure to the cooler and more vegetated microforest environment may be associated with higher HRV values and modest reductions in systolic and diastolic blood pressure compared with the impervious parking lot condition. Such findings would be consistent with improved autonomic balance and reduced cardiovascular stress during exposure to the vegetated environment.

In addition to cardiovascular measurements, the protocol includes biochemical indicators of stress physiology such as salivary cortisol and urinary catecholamines and their metabolites (secondary outcomes). We expect that exposure to the microforest environment may be associated with lower peak cortisol concentrations and reduced overall cortisol responses during the exposure period compared with the impervious environment. Urinary measurements of catecholamines and their metabolites provide additional indicators of sympathetic nervous system activation. Exposure to the microforest environment may therefore be associated with lower concentrations of norepinephrine and epinephrine metabolites relative to the parking lot condition, reflecting reduced activation of the sympathetic stress response during exposure to the vegetated setting. We also expect that participants exposed to microforest environments may report lower levels of acute anxiety, reduced perceived distress, and lower rates of rumination as reflected by their scores on validated questionnaires of stress and emotional state.

Although a substantial body of literature demonstrates that exposure to green environments is associated with reduced stress, improved cardiovascular function, and increased longevity [1], evidence is limited regarding whether compact, high-density greening interventions in highly built environments can generate meaningful physiological and ecological benefits. By integrating meteorological, clinical, and ecological assessments, the GRO Project provides a multidisciplinary assessment of how microforests can alter local environments and human physiology. Integrated analysis will examine whether differences in environmental exposures explain observed changes in cardiovascular and stress biomarkers (Aim 5). For example, mediation analyses will evaluate whether reductions in ambient temperature are associated with improvements in HRV or reductions in blood pressure, or whether lower exposure to pollutants is associated with changes in cortisol or catecholamine responses. By integrating environmental, physiological, and psychological measurements within the randomized crossover framework, the GRO Project will allow examination of potential pathways linking microclimate modification to acute cardiovascular and stress responses. Furthermore, longitudinal follow-up across multiple years (2025–) will capture the maturation of the microforest, permitting evaluation of both immediate and long-term impacts.

A key strength of this project is its ability to simultaneously assess microclimate modification and human health responses. Continuous monitoring of temperature, humidity, and air quality allows direct quantification of the extent to which dense plantings mitigate heat exposure and pollutant levels at the street scale (Exploratory Aim 3). This information is critical, as climate models predict rising urban heat exposure and associated health burdens in the coming decades [48]. By linking these data to individual-level cardiovascular and stress biomarkers, the GRO Project is designed to examine whether microclimatic improvements translate into measurable physiological resilience.

The layered planting design, which mimics natural forest succession, also provides an opportunity to evaluate the ecological services of urban microforests. Baseline surveys of avian species, soil microbial activity, greenhouse gas fluxes, and tree ecosystem services (Exploratory Aim 4) establish a robust ecological benchmark against which post-intervention changes can be assessed. Integrating these ecological metrics with meteorological and health data offers novel insights into the interconnections between biodiversity, environmental function, and human health.

Equally important, this project addresses questions of scale and replicability. While large urban parks have well-documented health and climate benefits, fewer studies have examined whether small, densely planted lots, common in land-constrained downtown areas, can generate similar effects. If successful, the GRO model is designed to generate data that may inform future scalability in urban contexts with similar density and land cover characteristics, particularly in neighborhoods with limited space, high impervious-surface coverage, and elevated vulnerability to heat stress.

The policy implications of this work are substantial. The results will inform municipal decision-making related to land-use codes, tree ordinances, and urban greening priorities. By demonstrating the environmental and health benefits of compact greening interventions, this study may support more widespread adoption of evidence-based planting practices that promote resilience, reduce pollution, and improve public health. Moreover, the [name] Microforest functions as both a community amenity and a living laboratory, strengthening engagement among scientists, planners, and the public.

In summary, the GRO Project provides a comprehensive, multidisciplinary framework for evaluating how small-scale, dense greening interventions affect urban microclimates, ecological function, and cardiovascular resilience. Findings from this project are expected to advance scientific understanding, inform policy, and offer a new framework for integrating nature-based solutions into the fabric of dense urban environments. As urban populations expand and climate stressors intensify, the importance of such targeted, evidence-based interventions will only grow.

## 4. Limitations and Future Directions

Despite its strengths, the GRO Project has several limitations. First, as a single-site intervention, findings may be influenced by the unique environmental and social context of downtown Louisville, which could limit generalizability to other urban areas with different climates, vegetation types, or community structures. The [name] Microforest’s species composition and density are tailored to Louisville’s temperate climate. Replication across diverse geographic and demographic settings will be necessary to confirm the broader applicability of microforest interventions, as ecological and microclimatic outcomes may vary in other settings. Second, while the randomized crossover design strengthens causal inference, acute physiological responses may not fully capture the long-term health benefits of greening. Repeated exposure over months or years may yield different or cumulative effects that extend beyond those observed during single visits. Planned longitudinal assessments will help address this gap, but continued follow-up will be important to gauge the durability of benefits as the forest matures. Third, long-term cardiovascular disease outcomes are not measured in this study design.

Lastly, while the environmental and ecological measurements are comprehensive, they may omit key mediators such as volatile organic compounds emitted by plants, microbial aerosols, or finer indicators of biodiversity. Incorporating additional measures, such as metabolomic or microbiome analyses of participants, could further elucidate mechanisms linking greenness and health. Finally, the project is resource-intensive, requiring specialized instrumentation, personnel, and ongoing maintenance. Widespread implementation of microforests will therefore require cost–benefit analyses and evaluations of scalability across different budgetary and governance contexts.

Despite these limitations, the GRO Project establishes a foundation for future research on how small-scale greening interventions affect community-level outcomes, including social cohesion, mobility, and perceptions of safety. Integration of environmental, health, and behavioral data with geospatial modeling could inform citywide strategies for optimizing greening. By extending research beyond physiological endpoints to include social and economic dimensions, future work can help build a comprehensive evidence base to guide urban policy and promote equitable health benefits from greening initiatives.

